## Abstract

**Background:**

Coronary heart disease (CHD) is highly prevalent amongst the South Asian communities in Britain. The reasons for this excess CHD risk are multifactorial, but in part relate to a susceptibility to diabetes mellitus - where the aberrant metabolism of non-esterified fatty acids (NEFA) and glucose are likely to underpin vascular disease in this population. Dietary intervention is an important and first line approach to manage increased CHD risk. However, there is limited information on the impact of the South Asian diet on CHD risk.

**Methods/Design:**

The Diabetes Health, Residence & Metabolism in Asians (DHRMA) study is a blinded, randomised, placebo controlled trial that analyses the efficacy of reduced glycaemic index (GI) staples of the South Asian diet, in relation to cardio-metabolic risk factors that are commonly perturbed amongst South Asian populations - primarily glucose, fatty acid and lipoprotein metabolism and central adiposity. Using a 10-week dietary intervention study, 50 healthy South Asians will be randomised to receive either a DHRMA (reduced GI) supply of chapatti (bread), stone ground, high protein wheat flour and white basmati rice (high bran, unpolished) or commercially available (leading brand) versions chapatti wheat flour and basmati rice. Volunteers will be asked to complete a 75g oral glucose tolerance test at baseline and at 10-weeks follow-up, where blood metabolites and hormones, blood pressure and anthropometry will also be assessed in a standardised manner.

**Discussion:**

It is anticipated that the information collected from this study help develop healthy diet options specific (but not exclusive) for South Asian ethnic communities.

Trial registration

Current Controlled Trials ISRCTN02839188

## Background

Coronary heart disease (CHD) is the leading cause of mortality and morbidity amongst South Asians living in the UK (people originating from the Indian subcontinent), who have a 50% greater risk of dying prematurely from this affliction than the general population [1,2]. This increased CHD risk is multifactorial, but in part is likely to be influenced by diabetes mellitus [3], which is more common amongst South Asian groups [4]. Indeed, CHD risk in South Asians is coordinated with the frequent clustering of metabolic risk factors that includes aberrant glucose and lipid metabolism[5,6], which may represent the commonality between diabetogenesis and atherogenesis in this population. These metabolic risk factors are recognised to be associated with more advanced atherosclerotic vascular disease [7] and increased cardiovascular mortality [8,9].

There is an urgent need for effective 'targeted' approaches in the prevention and management of CHD and the associated metabolic risk in South Asians. Dietary intervention remains a 'first line' approach to manage this increased risk. While dietary health promotion approaches to the management and prevention of CHD is availible for South Asians (i.e diet leaflets and health DVDs, websites such as South Asian health [10]), much of the scientific evidence that such material is based upon uses findings in populations other than South Asians. For South Asian diabetics, general health promotion material has had limited impact [11]. South Asians have also been excluded from major diabetes and cardiovascular clinical trials [12]. Reasons for this are complex, and it is not clear what the range of contributory factors are, what are the main reasons and whether the real issue is one of 'planned exclusion', 'inadvertent exclusion', 'non-participation' or a mixture of these. There is a need to increase South Asian participation in research.

### Dietary transition and cardiovascular risk in South Asians

The present study [DHRMA] was specifically developed to advance findings from an epidemiological study of CHD risk in a population of Indian migrants living in the UK. In this study, nutritional intake, lifestyle, glucose tolerance and CHD risk were compared between Indians living in Sandwell (UK) and their contemporaries still living in villages of origin in rural India [13]. While diabetes prevalence was generally high (15% irrespective of site), in India it was less frequently accompanied by metabolic CHD risk factors such as raised triglycerides and central obesity. The greater metabolic-CHD risk amongst the migrant Indians was underpinned by dietary change, a transition towards higher energy and fat intake at the expense of carbohydrate. Data also suggested a background of higher glucose excursions and unregulated NEFA metabolism in Indian populations [14], which has been reported elsewhere as ethnic differences in NEFA profiles following oral glucose challenges [15]. NEFA metabolism may be a key driver for the major CHD risk of these communities, through its role on lipid metabolism and hepatic insulin resistance [16].

### Glycaemic index in South Asian foods

Reducing postprandial glucose and NEFA concentrations may be a desirable option in the dietary management of metabolic-CHD risk in South Asians [17]. In recent years the 'glycaemic index' (GI) (a ranking system for carbohydrates based on their immediate effect on blood glucose levels) has emerged as a classification system for carbohydrate-containing food, where consumption of high GI meals in comparison with energy- and nutrient-controlled low GI foods are adversely associated with glucose intolerance [18]. The GI of foods relates to the nature of monosaccharides, starches, fat, protein and fibre it contains, and the method with which it is cooked. Typically, stone-ground breads have a low GI (high protein and fibre), which is why stone-ground chapatti flour is also likely to have a low GI, compared to other more refined versions (devoid of bran). Basmati rice has a high amylase content, which confers a low GI, and a higher bran content is likely to lower GI further, especially in an unpolished (i.e. high bran) preparation. Importantly, low GI foods are shown to reduce hyperglycaemia, hyperinsulinaemia and postprandial circulating NEFA [19]. While South Asians resident in Britain have varied diets (influenced by culture, religion and British culture), many migrants still subscribe to diets that include staples of carbohydrate such as breads (chapatti, roti, naan) and rice [20]. The industrialisation of food processing and relative affluence has promoted the consumption of more refined foods (high GI) both in India and the UK. In South India [21], postprandial glucose excursions were favourably delayed by staple foods prepared and eaten there, but these foods have yet to be assessed in Britain amongst Indian migrant populations.

### Objectives and hypothesis of DHRMA

The purpose of DHRMA is to provide the scientific basis to help regenerate cultural traditions in food intake, with the aim to develop dietary CHD management options, specifically tailored (but not exclusively) for people of South Asian origin living in the UK. DHRMA is a novel project, as these foods are not commercially available, and the study plan is based on pilot findings from our own research and developed with experience from our ongoing programme of CHD risk screening in ethnic minorities (Healthy Hearts), where 900 individuals have been assessed using a community based approach. [22]

### Objectives are as follows

(i) to establish the GI of existing (ie. produced in the UK) traditional, and regenerated (see (ii)) food staples of South Asian cuisine (specifically chapatti flour and basmati rice).

(ii) to develop will DHRMA test foods that have been specifically that are processed in a similar fashion to those available in rural India: basmati rice that is polished to a low level (less bran removed, grain quality distribution ratio score by KETT (Tokyo, Japan) of <35%)*, and stone-ground chapatti flour with added grains (oats, barley and chick pea).

(iii)to determine the efficacy of low GI DHRMA foods on indices of diabetes and CHD risk using a blinded, randomised controlled trial.

Note* KETT is an industry standard originating from Japan - a score based on the whiteness of rice. Generally amongst basmati rice sold in the UK, this score is around 40-44%.

The DHRMA study will focus on testing the hypothesis that a 10-week supply of DHRMA foods (reduced GI supply of chapatti stone ground, high protein wheat flour and high bran, unpolished white basmati rice) to healthy South Asians will result in favourable changes in cardio-metabolic risk factors (glucose tolerance, fatty acid, triglyceride and HDL cholesterol metabolism and central adiposity) as compared those randomised to commercially popular (market leaders) versions of chapatti flour and white basmati rice.

## Methods/Design

Ethical approval for the study was provided by North Staffordshire Research Ethics Committee (REC reference 08/H1204/130), and all prospective volunteers for the DHRMA study will undergo an informed consent process. The DHRMA study is split into two parts, (i) the assessment of glycaemic index in Indian foods and (ii) a dietary intervention trial.

### Development of DHRMA low glycaemic index foods

The Study will be undertaken in the area of Sandwell and West Birmingham, at Sandwell and West Birmingham Hospitals NHS trust (UK). Healthy volunteers (body mass-index between 18-25 kg/m^2^, no known cardiovascular disease or associated medication, normal glucose tolerance) will be approached for this study from local communities [22] as well as hospital staff. The GI will be measured using FAO/WHO expert consultation (1998) guidelines. Briefly, an eight point capillary blood glucose profile will be measured over a 2 hour period (i.e. 15 min intervals) following the administration of a 50 g glucose load in each prospective volunteer after an overnight fast. Volunteers will then be invited for repeat visits where a 50 g glucose equivalent from test foods will be administered (done in triplicate for as recommended by the FAO/WHO guidelines).

The preparation of chapattis (ingredients, size and cooking time) and rice (water added and cooking time) will be standardised by researchers and subjects will be advised a standard level of activity during the study period. The test foods will be eaten over 15 minutes with water. Capillary blood samples will be analysed using a standard capillary glucose monitor (quality assurance monitored, Roche Accutrend GC, Roche UK). A capillary blood glucose response for curve for each test food will be plotted, and with each subject, the GI for the food will be the proportion of this area as a percentage of the response to 50 g of glucose.

### Interventional trial

This is a 10-week, blinded, parallel, randomised intervention trial in South Asians either DHRMA versions of stone ground chapatti flour and high bran white Basmati rice or the commercially popular white chapatti flour (Elephant atta, Premier Foods, UK) and white Basmati (Tilda, UK) will be supplied to participants.

The Inclusion criteria will include age <55 yrs, BMI <30 kg/m^2^, systolic/diastolic BP <140/90 mmHg (no antihypertensive use), South Asian ethnicity and use of chapatti flour or rice as part of their normal diet (>3 times a week) and >50% of energy derived from carbohydrates and <30% from fat - determined by 4-day food diaries, used previously [13]).

A total of 50 subjects will be randomised onto either arm in a blinded fashion, and supplied with study carbohydrates (see Figure 1). The study carbohydrates will be packaged by our industrial collaborator (East End Foods, UK), who randomise and allocate individual packet numbers to each test food (information relating to the contents will be stored with our collaborator and so blinded to study researchers and the study participants). The supply of rice and flour will be in clear, unlabelled 15 kg bags packaged within a white box with an assigned randomisation number and trial details. Random number allocation will be through a computer generated system, with no provision for factorisation.

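### Withholding the contents code does not conceal foods that differ visibly, so participant blinding is not secured, and the commercial-food control is not a placebo

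*Protocol article*

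**What the plan says.** The Methods/Design paragraph of the abstract states that the study "is a blinded, randomised, placebo controlled trial". The Interventional trial section repeats that it is blinded and says how: the collaborator packs the food, numbers the packets and keeps the key, with "information relating to the contents will be stored with our collaborator and so blinded to study researchers and the study participants". On packaging, the same section says: "The supply of rice and flour will be in clear, unlabelled 15 kg bags packaged within a white box", and the box carries a randomisation number.

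The intervention arm receives "DHRMA versions of stone ground chapatti flour and high bran white Basmati rice". The control arm receives a named commercial white chapatti flour and a named commercial white basmati.

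The objectives section gives the test rice a KETT score below 35% and explains that KETT is "a score based on the whiteness of rice". It puts basmati sold in the UK at around 40-44%. The test flour is stone-ground and has oats, barley and chick pea added.

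Participants qualify by using chapatti flour or rice more than three times a week.

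**The concern.** The stated mechanism protects the allocation list. Blinding a participant to a food also requires that the food does not reveal itself, and this food is handled, cooked and eaten at home for 10 weeks. One of the specified differences between the arms is a whiteness score, and another is the grain content of the flour.

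A participant who guesses the arm may change the rest of the diet, the amount of study food eaten, what goes into the 4-day dietary record, or the decision to return at 10 weeks. Diet records, adherence and dropout are directly exposed. Anthropometry and blood pressure are exposed too if the person measuring learns the arm. Laboratory assays resist measurement bias, but glucose and triglycerides still respond to changed behaviour. An effect that arises partly this way would be reported as coming from a blinded, placebo-controlled comparison.

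The placebo label raises a separate problem. The control is an ordinary staple with its own metabolic effect. The contrast is therefore between two foods, and not between a food and an inert substance.

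**Working it through.** The point rests on comparing statements and on one subtraction. The sample size of 25 per arm plays no part in it.

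**1. What is concealed, and from whom**

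| Step | What the article describes | What it conceals |
|---|---|---|
| Key to packet numbers | Held by the collaborator | The allocation list, from everyone else |
| Outer packaging | White box bearing a number | The contents, from anyone handling a closed box |
| Inner packaging | Clear bag with no label | The brand name, but not the appearance |
| Cooking and eating | Done by the participant over 10 weeks | Nothing |

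Concealment from staff can last as long as the box stays closed. Concealment from the participant ends when the box is opened, unless the foods are alike.

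**2. Are the foods alike by their own specification?**

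*Rice.* The inputs come from the objectives section: test rice below 35, and UK basmati generally about 40 to 44.
- Against the lower end: 40 − 35 = 5, so the gap is more than 5 points.
- Against the upper end: 44 − 35 = 9, so the gap is more than 9 points.

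These are lower bounds, because 35 is a ceiling for the test rice. They assume that the control brand lies in the general UK range, since its own score is not given.

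*Flour.* The test flour is stone-ground wheat with three added grains or pulses. The control is described as white. No numerical measure of appearance is given for either.

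*Matching.* The article describes no matching for colour, texture or taste.

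**3. Does the participant have a reference point?**

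Each participant sees only one arm's food, but eligibility requires regular use of at least one of the two staples. The section on objectives and hypothesis says the test foods cannot be bought, while the controls are market leaders. A control participant may therefore receive something familiar and an intervention participant something unfamiliar.

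**4. Can researchers recognise the foods?**

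The glycaemic index part covers both existing and regenerated staples, and there "The preparation of chapattis (ingredients, size and cooking time) and rice (water added and cooking time) will be standardised by researchers". Some researchers will therefore know what the foods look like. The article does not say whether they also measure outcomes in the trial. The remaining routes are a clear bag seen outside its box, or a participant describing the food at follow-up.

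**5. Is the control a placebo?**

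The abstract uses the word. The next sentence of the abstract, the stated hypothesis and the Interventional trial section all describe leading commercial flour and rice. These statements conflict, and the description of the foods is the specific one.

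**The case against.** The strongest reply has four parts.

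- **No description of appearance.** The article never says how the products look, cook or taste, and it calls both rices white basmati. It gives no threshold at which a consumer would see a KETT difference. This stands: recognition is a reasoned expectation and not a documented fact.
- **Parallel arms and unlabelled bags.** Nobody sees the two versions side by side, brand cues are gone, and finding a food unusual is not the same as knowing one's allocation. This weakens the point without removing it, because regular users bring their own standard of comparison. The eligibility rule says flour or rice, so a participant need not be familiar with both.
- **Staff.** A reader might infer that researcher blinding is bound to fail. The documents do not support that. A closed, numbered box can keep staff blinded, nothing has assessors opening bags, and overlap between the food-preparation staff and the outcome assessors is not stated. For researchers this is a vulnerability only.
- **Limited impact.** The main measures are laboratory ones, and the placebo label appears only in the abstract, beside a correct description of the control. Both facts limit the harm. They do not make either label correct, and behaviour can still reach laboratory results indirectly.

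How boxes are handed over and how staff are organised may well be set out in the full protocol, so their absence from the article is not counted against it.

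**Conclusion.** The point holds for participants and for the label. The article claims participant blinding on the strength of a withheld code, while specifying foods that differ in visible attributes and that participants must open, cook and eat. Participant blinding is not secured by what is described. Researcher blinding is attainable but vulnerable. The control is an active commercial food.

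The only figure available is a whiteness gap of more than 5 to 9 points, on the assumption that the control rice is typical of UK basmati. A reader might go further and conclude that blinding cannot hold at all, or that most participants would identify their arm. Neither follows: the appearance of the products is undocumented, and no recognition rate or size of bias can be derived. Randomisation, the choice of foods and the laboratory measurements are unaffected. What changes is the strength of the claim the trial can make, above all for diet records, adherence, dropout and outcomes that depend on behaviour.

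**What to change.** 1. Replace the blinded, placebo-controlled description with: outcome-assessor- and laboratory-blinded, commercial-food-controlled. Do not claim participant blinding.
2. Limit conclusions on diet records, adherence, dropout and behaviour-sensitive outcomes to what a trial without secured participant blinding can support.
3. Use opaque inner bags in sealed boxes, so that staff do not see the contents. This protects staff only; it cannot blind someone who cooks the food.
4. At the 10-week visit, record each participant's and each assessor's guess of the arm, and report the guesses by arm.

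The cost is different bags, one extra question at follow-up and a slightly weaker blinding claim. The foods, the randomisation and the sample size stay as they are.

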**Figure 1 F1:**
[figure not shown]
**Study Flow-chart**.

Each participant will be asked to attend three visits (screen, randomisation and follow-up). The screening visit will be used to initiate the consent process blood, and to assess inclusion criteria (eg dietary intake).

At randomisation and follow-up, blood pressure and anthropometry will be measured and an OGTT will be performed. Subjects will also be asked to complete a 4-day dietary record at randomisation and follow-up. The main metabolic measures will be 10 week changes in - OGTT metabolites and hormones (glucose, insulin, NEFA), adiponectin, leptin and lipids and lipoproteins (including serum triglycerides and HDL cholesterol).

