### Power calculation

The sample size was calculated on the results from our migration study [13] and dietary intervention study [23] where we found a 0.56 (SD = 0.34) fall in CHD risk using the biomarker C-reactive protein for individuals on the substitution dietary intervention and no significant reduction in the other groups. Using a paired t-test, at 80% power, α<0.05, 25 subjects/arm will allow the detection of a 1 mmol difference in 2 hr glucose and 0.15 mmol change in NEFA suppression (this is ½ the difference seen between glucose tolerant and intolerant Indian Gujaratis in our migration study [14]).

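### The main measures are framed as 10-week changes and the only test named works on unadjusted change; the between-arm analysis should be stated with baseline as covariate

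*Protocol article*

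**What the plan says.** All references are to the protocol article.

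- **Form of the outcome.** Interventional trial, text after Figure 1: "The main metabolic measures will be 10 week changes in" OGTT metabolites and hormones, adiponectin, leptin, and lipids and lipoproteins.
- **Baselines.** The same text: "At randomisation and follow-up, blood pressure and anthropometry will be measured and an OGTT will be performed". The Abstract (Methods/Design) confirms that the OGTT takes place "at baseline and at 10-weeks follow-up, where blood metabolites and hormones, blood pressure and anthropometry will also be assessed". Each main measure is therefore taken before and after the intervention.
- **Test.** Power calculation: "Using a paired t-test, at 80% power, α<0.05, 25 subjects/arm". The targets are "will allow the detection of a 1 mmol difference in 2 hr glucose" and "0.15 mmol change in NEFA suppression". No other test is named in the article.
- **Comparison.** The hypothesis (end of the Objectives) and the parallel two-arm design (Interventional trial) set the study foods against commercial versions, with 50 people in total.
- **Allocation.** It is computer-generated and, as I read the Interventional trial section, unstratified.

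The article gives no between-arm analysis model. It neither mentions nor excludes baseline adjustment.

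**The concern.** A change outcome together with a paired t-test points a reader towards subtracting baseline and stopping there. That has two weaknesses.

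1. **Fit.** A paired test within one arm does not compare the arms, and the hypothesis is a comparison of arms.
2. **Efficiency and imbalance.** Even when changes are compared between arms, subtraction in effect fixes the slope on baseline at 1. For a noisy measure the true slope is lower, so the change score carries avoidable variance. It also passes chance baseline differences into the estimate through regression to the mean. With 25 per arm and no stratification, such differences are to be expected.

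At stake is precision that the trial has already paid for by measuring everyone twice.

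**Working it through.** **Inputs from the article:** 25 per arm, 80% power, alpha 0.05, targets of 1 mmol (2 h glucose) and 0.15 mmol (NEFA suppression).

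**Assumptions:** two-sided testing; equal outcome variance s² at both visits; rho from 0.3 to 0.7. The article gives neither rho nor an SD for glucose or NEFA.

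**Step 1. The plan's own figure.** The 25 per arm cannot be reproduced, because neither target effect has an SD. The one effect and SD pair in the section is a "0.56 (SD = 0.34) fall in CHD risk using the biomarker C-reactive protein". It gives 0.56/0.34 = 1.65 SD, which needs about 6 subjects for a paired test or 7 per arm for a two-sample test. So I solved for the SD of change at which 25 gives 80% power for 1 mmol (noncentral t):

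- Case A, within-arm paired test (noncentrality √25/SD, 24 df): SD = 1.71 mmol.
- Case B, two-sample test on change (noncentrality √(25/2)/SD, 48 df): SD = 1.24 mmol.

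The matching NEFA SDs are 0.257 and 0.185, and the powers below are the same for NEFA.

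**Step 2. Between-arm power with unadjusted change.**

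- Case A: noncentrality 3.536/1.71 = 2.07; power 52.5%.
- Case B: 80% by construction.

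**Step 3. Variance ratio.** Per subject, Var(change) = 2(1−rho)s² and Var(adjusted) = (1−rho²)s². The ratio is (1−rho²)/[2(1−rho)] = (1+rho)/2.

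**Step 4. Adjusted power at 25 per arm** (SD multiplied by √((1+rho)/2), 47 df):

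| rho | Variance ratio | Variance reduction | Case A: from 52.5% to | Case B: from 80% to |
|---|---|---|---|---|
| 0.3 | 0.65 | 35% | 70.8% | 93.5% |
| 0.5 | 0.75 | 25% | 64.6% | 89.9% |
| 0.7 | 0.85 | 15% | 59.2% | 85.9% |

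In sample-size terms, 1/0.65 = 1.54, 1/0.75 = 1.33 and 1/0.85 = 1.18, so the gain equals about 54%, 33% or 18% more subjects.

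**Step 5. How much of the Case A shortfall this returns.** The shortfall is 80 − 52.5 = 27.5 points. Adjustment returns 18.3 points (67%) at rho 0.3, 12.1 (44%) at 0.5 and 6.7 (24%) at 0.7. At rho 0.9 it returns 2.1 points (8%). For 80% power in Case A, unadjusted change needs 48 per arm; the adjusted model needs 31, 36 or 41.

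**Step 6. Chance imbalance (Case A SD).** From SD of change = s√(2(1−rho)), s = 1.71/√1.4 = 1.45 at rho 0.3 and 1.71/√0.6 = 2.21 at rho 0.7. One standard error of the baseline difference is s√(2/25), that is 0.41 or 0.62 mmol. Given such an imbalance, the change-score contrast shifts by (1−rho) times it: 0.7 × 0.41 = 0.29, or 0.3 × 0.62 = 0.19 mmol. That is about a fifth to over a quarter of the 1 mmol target. The adjusted model removes this shift.

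**The case against.** The strongest reply is that the article does not fix an unadjusted analysis at all. "Using a paired t-test" appears once, under Power calculation, and explains how the number of subjects was reached. The sentence on 10-week changes defines what is measured, not the model. Change regressed on arm and baseline gives the same treatment estimate and standard error as the 10-week value regressed on arm and baseline, so the remedy is compatible with the text. A full protocol or SAP, not shown here, may already specify it.

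Much of this stands, and it rules out several stronger readings that a reader might infer:

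- **That a paired t-test is the planned efficacy analysis.** The article names it for sizing only.
- **That the trial has 53% power.** That figure depends on an SD of 1.71, which is back-solved and not in the article. If the 25 per arm came from a two-sample calculation, power on raw change is already 80%.
- **That adjustment recovers most of the lost power.** This holds only at low rho. The fall from 80% to 53% also comes from sizing a parallel trial with a paired test, not from the use of change scores.
- **That a change-score comparison is invalid.** Under randomisation it is unbiased on average. The shift in Step 6 is conditional on the imbalance that happens to occur.

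What does not stand is that nothing is left to correct. The article goes beyond silence: it commits to an outcome form and names one test, and that test does not address the stated between-arm hypothesis. A better method needs no new data and gains under either account of the sample size.

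**Conclusion.** The point holds as a recommendation on efficiency and clarity; it does not show the planned analysis to be invalid. The stated outcome form and the only named test both rest on unadjusted change, while the question is a between-arm one and all baselines are available.

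Baseline adjustment lowers the variance by 35% to 15% for rho of 0.3 to 0.7, assuming equal variances at both visits. At 25 per arm, power for 1 mmol goes from about 53% to between 71% and 59% on the paired-test account, or from 80% to between 93.5% and 85.9% on the two-sample account. The direction of the gain is secure. Its size depends on rho and on the SD, neither of which the article gives.

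The sizing of a parallel trial by a paired test remains a separate fault. On the paired-test account, power stays below 80% over the whole assumed range of rho even after adjustment.

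**What to change.** State in the analysis wording that, for each main measure, the arms are compared with a linear model of the 10-week value (or, equivalently, the 10-week change) on randomised arm, with that measure's baseline value as covariate. Report the adjusted between-arm difference with a 95% CI, and keep raw change from baseline as a descriptive summary. If the full protocol or SAP already says this, a cross-reference is enough.

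The cost is a change of wording and one degree of freedom per model, with no extra subjects, visits or assays. The sample-size justification should be redone separately on the between-arm difference, with stated SDs for 2 h glucose and NEFA; any allowance for baseline adjustment there needs a stated rho.
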